### 2.5. Pilot Study

Prior to the implementation of a digital prenatal physical activity program utilizing SMS text messages for inclusion into the MomConnect health device to improve physical activity behavior during pregnancy, which is the expected outcome measure of this study, a pilot study of 20 reproductive-age women will be conducted to determine the comprehension and effectiveness of the prenatal physical activity SMS prototypes. The criteria for selection in the pilot study will be women who are aged 18–45 years, able to speak English and isiXhosa, and engaged in at least 30 min of moderate activity five days a week (more than 150 min) in the preceding week (self-reported) [38]. The participants in this phase will be asked to indicate whether they understand the relevance (content), preferred timing, and frequency of the prenatal physical activity SMS prototypes. The feedback from the outcome of the pilot study will be used to restructure the content, timing, and frequency of the prenatal physical activity SMS prototypes.

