### 2.3. Phase 2: Assessment of Prototype Prenatal Messaging

During Phase 2, prototype text messages will be developed for each of the categories identified in Phase 1. Prototype text messages will provide mobile-friendly access to the MomConnect network and will be limited to 150 characters or fewer. Next, we will conduct interviews to ascertain the perceived preference and acceptability of the prenatal physical SMSs within the context of the setting [38]. A convenient sample of prenatal care providers, including physicians, nurses/midwives, and sedentary pregnant women who do not meet the recommended 150 min of moderate-intensity physical activity per week, will be interviewed. Participants in the interviews will be recruited in health facilities. Participants must be (i) a doctor, nurse/midwife, or pregnant patient at antenatal health facility, (ii) able to speak English and isiXhosa, and (iii) at least 18 years old to be eligible for the study. In-person interviews in a quiet designated place provided in each of the health facilities by the facility manager. Participants will be provided with three prototype text messages for each developing category. The interviewer will present the text messages to the participants and then ask the following questions [38]:Would you be able to share your perspective on the text messages?Do you believe these messages would support women in increasing their physical activity?What improvements do you believe could enhance the messages?Which SMS message, out of all of them, would you prefer, and why?

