The findings of this study will assist in ascertaining the preferred dose of SMS messaging to promote prenatal physical activity and exercise among women. Similarly, the results of this study will provide the foundation for designing a randomized control trial to evaluate the effectiveness, efficacy, and acceptability of MomConnect in promoting prenatal physical activity among pregnant women within the framework of BCCM. If the MomConnect interventional approach proves effective, it could lead to a large-scale implementation among reproductive-age women in the province and across the country. Such information is necessary for strategic planning regarding the delivery of prenatal physical activity healthcare services. Finally, the findings of this study will assist policymakers in comprehending the significance of developing an innovative, low-cost intervention strategy to enhance prenatal physical activity and exercise, a frequently overlooked yet crucial aspect of antenatal healthcare.

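### The pilot claims to determine message effectiveness that it does not measure, and takes its feedback from already-active women who need not be pregnant

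*Protocol article*

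**What the plan says.** Section 2.5 (Pilot Study) fixes four things.

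- **Aim.** Before the programme is implemented, "a pilot study of 20 reproductive-age women will be conducted to determine the comprehension and effectiveness of the prenatal physical activity SMS prototypes".
- **Entry.** "The criteria for selection in the pilot study will be women who are aged 18–45 years, able to speak English and isiXhosa", and also "engaged in at least 30 min of moderate activity five days a week (more than 150 min) in the preceding week", by self-report. Neither current nor past pregnancy is a criterion.
- **Data.** Participants are "asked to indicate whether they understand the relevance (content), preferred timing, and frequency of the prenatal physical activity SMS prototypes".
- **Use.** The feedback "will be used to restructure the content, timing, and frequency of the prenatal physical activity SMS prototypes".

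Other sections bear on this. In Section 2.3 the Phase 2 assessors are care providers and "sedentary pregnant women who do not meet the recommended 150 min of moderate-intensity physical activity per week". Section 2.4 surveys 200 conveniently selected women, currently or previously pregnant, on five frequency options and three times of day. Section 2.7 plans descriptive summaries for the quantitative data. Table 1 has no row for the pilot. The Discussion says that the study's results "will provide the foundation for designing a randomized control trial to evaluate the effectiveness, efficacy, and acceptability of MomConnect".

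**The concern.** The aim, the entry criteria, the data and the use of the pilot do not fit together.

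First, effectiveness of messages meant to raise activity is a claim about behaviour. The pilot asks about understanding and records no behaviour. A report that kept to the stated aim would have to make an effectiveness statement with no data behind it.

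Second, the messages are for pregnant women, in a province where the Introduction describes activity as low. A pilot sample that is active by criterion and need not be pregnant may find the content clear and the schedule acceptable for reasons that do not carry over to those users. This is described as a step before implementation, and it leads directly to changes in the messages, so the mismatch would pass into the product.

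**Working it through.** The article gives no derivation for the 20 pilot women or for the 200 survey women: no precision target, effect size or power. There is no stated figure to reproduce, and no sample-size error is claimed. Most of the check is a comparison of stated rules.

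**1. Aim against data.** The aim has two parts, comprehension and effectiveness. The items collected (Section 2.5) cover understanding of relevance, timing and frequency. They serve the first part only. An effectiveness statement would need at least an activity measure and something to compare it with. Section 2.5 gives no activity outcome, comparator or follow-up; Section 2.7 and Table 1 add none. The Discussion places evaluation of effectiveness in a later randomised trial.

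**2. Entry against target.** The activity criterion gives a floor of 5 × 30 = 150 min per week. (The bracketed gloss says more than 150, but the stated minimum gives exactly 150.) So 20 of 20 entrants are at or above the level that Phase 2 uses to define sedentary women. Had activity been measured, none could move from below target to target.

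**3. Pilot against the other groups of women.**

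| Group | Pregnancy | Activity |
|---|---|---|
| Phase 1 interviews (2.2) | current or past | at target |
| Phase 2 patients (2.3) | current | below 150 min/week |
| Phase 3 survey (2.4) | current or past | no criterion |
| Pilot (2.5) | not required | at target |

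The pilot repeats the Phase 1 activity criterion. In Phase 1 it has a purpose, because active women are asked why they are active. In a late check of messages for pregnant women it excludes every user below target. The pilot is also the only group of women with no pregnancy criterion.

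**4. Precision, if pilot and survey answers on frequency or timing are ever weighed against each other.** The half-width of a 95% interval for a proportion is 1.96 × √(p(1−p)/n). The values of p are assumptions.

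| p | n = 20 | n = 200 |
|---|---|---|
| 30% | 20.1 points | 6.4 points |
| 50% | 1.96 × √(0.25/20) = 21.9 points | 1.96 × √(0.25/200) = 6.9 points |
| 80% | 17.5 points | 5.5 points |

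Exact 95% intervals at 50% are 27.2% to 72.8% with 20 women and 42.9% to 57.1% with 200. The ratio of widths is √(200/20) = 3.2 whatever the value of p. These figures treat both samples as random. The survey is a convenience sample, and the article does not say how the pilot women are drawn, so the figures describe sampling noise only and not selection bias.

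**The case against.** Several points on the other side have force.

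- **The intended users are pregnant women in general, not only inactive ones.** This stands. The Abstract, Introduction and Discussion speak of pregnant women, the Discussion looks ahead to use among reproductive-age women, and Phase 3 sets no activity criterion. Active pregnant women therefore need not be excluded from the pilot. The fault is that only active women may enter and that pregnancy is not required.
- **Sedentary pregnant women already assess the messages in Phase 2.** This also stands, and it limits the harm. But the pilot has authority to change the messages, and Section 2.5 does not send the changes back to that group.
- **Nobody plans an effectiveness endpoint, and the Discussion leaves it to a trial.** True, which is why the word should go. A reader might infer that a pilot effectiveness estimate will feed the design of the randomised trial. No section says so.
- **The pilot does not overrule the survey.** A reader might infer that 20 women will reset a schedule chosen by 200. The documents do not support this as a fact. Section 2.5 says only that the pilot precedes implementation. That it follows Phase 3 is inferred from section order and from Phase 3 being where frequency and timing are determined. The text speaks of restructuring, with no rule for replacing survey results. The pilot question can be read as a check of understanding and not as a second vote.
- **Simulating how often 20 women would pick the wrong favourite frequency proves little.** Agreed. The result depends on assumed preference shares and on a most-votes rule that the article does not contain, so the conclusion does not rest on it.

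Twenty women is also not too few for a comprehension check.

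**Conclusion.** Two points hold on the text of Section 2.5 alone. The pilot can support comprehension and perceived relevance, and its stated aim of determining effectiveness has no outcome, comparator or follow-up behind it. Its entry criteria admit only women already at target (20 of 20) and do not require pregnancy, so feedback that changes content, timing and frequency does not come from a sample defined by the intended use, and comes from the opposite side of the activity threshold to the Phase 2 patients.

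A third point is conditional. If the pilot follows the survey, feedback on frequency and timing from 20 women is about 3.2 times less precise than the survey's (21.9 against 6.9 points at an assumed 50%, under random sampling), and the article does not say how the two are to be weighed.

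These are faults in stated rules, not detail left to a fuller document. The study is formative and tests no hypothesis, so this should be fixed but does not undermine the study as a whole.

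**What to change.** In Section 2.5:

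1. Replace effectiveness with perceived relevance in the aim, and state that effectiveness is left to the randomised trial foreseen in the Discussion.
2. Require pilot participants to be currently pregnant, and include women below 150 min of moderate activity per week, as in the Phase 2 patient definition. Active pregnant women may remain.
3. State whether the pilot comes before or after Phase 3. If after, keep the survey as the primary basis for frequency and timing and use pilot feedback mainly for wording and content.

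The cost is a few sentences, with the number of women unchanged. The pilot gives up any effectiveness statement, and recruitment becomes slightly narrower because pregnancy is required. The change must come before pilot recruitment, because analysis cannot repair a sample drawn from the wrong group.

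### The pilot aims to determine comprehension of the SMS prototypes, but the only measure described is self-declared understanding, which misses misreading that the woman does not notice

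*Protocol article*

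**What the plan says.** Section 2.5 (Pilot Study) states that "a pilot study of 20 reproductive-age women will be conducted", with the purpose "to determine the comprehension and effectiveness of the prenatal physical activity SMS prototypes". The information to be collected is given in one sentence: "The participants in this phase will be asked to indicate whether they understand the relevance (content), preferred timing, and frequency" of the prototypes. The result has a defined use: "The feedback from the outcome of the pilot study will be used to restructure the content, timing, and frequency" of the messages. The section describes no content question, no restatement task, no scoring and no rule for when a message needs revision.

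The language criterion for the pilot is "women who are aged 18–45 years, able to speak English and isiXhosa". It covers speaking only, whereas section 2.4 also asks Phase 3 respondents to be able to read.

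In section 2.3, the Phase 2 interviews are held "to ascertain the perceived preference and acceptability of the prenatal physical SMSs". Their questions include "Would you be able to share your perspective on the text messages" and "What improvements do you believe could enhance the messages". The other two ask whether the messages would support activity, and which message is preferred and why.

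**The concern.** The aim and the measure do not match. Asking a woman whether she understands records her belief about her understanding. That belief is right when she knows she is confused and wrong when she has taken a different meaning from the one intended. The second case is what a comprehension check most needs to find, and a larger sample asked the same question would still miss it.

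At stake is the restructuring step. If nearly all women say they understand, the investigators have no signal that a message needs rewording, and an unclear message may stay as it is. This is a weakness in a method that the article states, rather than a detail it merely leaves out.

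**Working it through.** **Step 1: is comprehension tested anywhere else?** The article gives no figure to reproduce, so the first check is of the text, section by section.

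- Section 2.3 (Phase 2): the aim is preference and acceptability. The four questions seek perspective, perceived support, improvements and preference. None asks what a message means.
- Section 2.4 (Phase 3): the survey of 200 women asks for preferred frequency and time of day.
- Section 2.5 (pilot): comprehension is an aim; the measure is women indicating whether they understand.
- Section 2.7 (Data Analysis): thematic analysis of the Phase I and II interviews, and descriptive statistics on frequency and timing. No comprehension analysis is described.
- Table 1: outcomes are listed for Phases I to III; none is comprehension, and the pilot has no row.

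The pilot item is therefore the only measure described for comprehension.

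**Step 2: how far could self-report mislead with 20 women?** The article gives neither rate needed here, so both are assumptions, shown over a range:

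- n = 20 (section 2.5)
- q = share of women who misread a given message (assumed 0.10, 0.20, 0.30)
- s = share of those misreaders who say they do not understand (assumed 1, 0.5, 0.25, 0)

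Taking the women as independent, and assuming that only misreaders flag a message, the chance that nobody flags it is

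P(no flag) = (1 − q·s)^20.

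For example, q = 0.20 and s = 0.25 give (1 − 0.05)^20 = 0.95^20 = 0.358. With s = 1 the result is 0.80^20 = 0.012.

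| q | s = 1 | s = 0.5 | s = 0.25 | s = 0 |
|---|---|---|---|---|
| 0.10 | 0.122 | 0.358 | 0.603 | 1 |
| 0.20 | 0.012 | 0.122 | 0.358 | 1 |
| 0.30 | 0.001 | 0.039 | 0.210 | 1 |

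The s = 1 column stands for a check that detects every misreading, which is the best that scored restatement could achieve. The s = 0 column is the case where no misreader recognises her error; the message then always passes.

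**Step 3: effect on the reported proportion.** True comprehension is 1 − q and expected self-declared comprehension is 1 − q·s, so the overstatement is q(1 − s). Over the grid it runs from 0 (s = 1) to 30 percentage points (q = 0.30, s = 0). In whole women: if 6 of 20 misread and 5 of those 6 say they understand, the pilot shows (14 + 5)/20 = 95% against a true 14/20 = 70%.

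These figures show the direction and mechanism. They are not estimates for this trial.

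**The case against.** The strongest reply is that one sentence in a condensed article is not the instrument. The pilot form is not shown and may hold content questions. That limits certainty, but the article does not leave the method open: it names self-declared understanding as what will be asked, and nothing beside it for comprehension.

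Second, Phase 2 is not worthless here. Physicians, nurses or midwives and sedentary pregnant women see three prototypes per category and answer open questions, so a misreading or an ambiguous phrase may come to light. This stands. It is incidental, however, because those interviews are aimed at preference and acceptability.

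Third, a reader might infer that the pilot item is incoherent, since a preferred timing is stated rather than understood. This is largely loose grammar. The sentence can be read as asking whether women understand the content and which timing and frequency they prefer. On that reading, comprehension is still self-declared.

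Fourth, a reader might infer that courtesy towards an interviewer inflates the answers. Section 2.5 mentions no interviewer and does not say how the pilot is administered, so the point should not rest on this.

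Fifth, a reader might infer that a high rate of yes answers would be taken as proof of comprehension and that misread advice would then reach MomConnect unchanged. The article does not support this. It sets no pass rule and uses the feedback formatively. The Discussion speaks only of potential integration and foresees a randomised trial, with large-scale implementation to follow only if the approach proves effective.

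**Conclusion.** The point holds in a limited form. For the aim of determining comprehension, the article describes a measure that cannot detect unrecognised misreading, and no other phase is designed to do so. The pilot could overstate comprehension and leave unclear messages unrevised at the restructuring step. The size is unknown: the overstatement ranges from nothing to 30 percentage points over the assumed rates, and the document favours no value within that range. The conclusion rests on reading the pilot sentence as a fair summary of the instrument; objective items in an unseen form would answer it. It does not depend on the illustrative rates, on an interviewer being present, or on any claim about what finally enters MomConnect. Since the remedy is cheap and serves a stated aim, it is worth making before the pilot starts.

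**What to change.** For each message, ask each of the 20 women to say in her own words what it tells her to do. Score the answer as correct or incorrect against a key of intended meaning written before the pilot, and let incorrect restatements trigger revision of that message. If a numerical cutoff is wanted, the investigators should set it in advance and treat it as a working rule: with 20 women even 16 correct has an exact 95% interval of about 56% to 94%, so a cutoff separates clear from unclear messages only weakly. Ask perceived relevance, preferred timing and preferred frequency as separate items, and state in section 2.5 how understanding will be checked.

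The cost is a few more minutes per participant and a short scoring key. The sample size does not change.

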### 2.6. Recruitment Potential Challenges

This study may face recruitment challenges such as privacy and confidentiality concerns, technological barriers, and fear of stigmatization. These challenges will be addressed through clear explanations of data collection, storage, and usage, provision of written and verbal informed consent in a comprehensible language for the participants, engagement in culturally sensitive communication to respect the participants’ values and beliefs, and implementation of anonymization techniques alongside secure data storage methods.

### 2.7. Data Analysis

We will perform qualitative analysis using the thematic content analysis approach for Phases I and II, based on the qualitative interview data from the pregnant/non-pregnant women and the healthcare providers (physicians, midwives, and nurses). The individual interview transcripts will be analyzed using Atlas.ti 12.0. Descriptive analysis (frequency, percentages, mean, and standard deviation) will be applied to the quantitative data to summarize the variables related to the frequency of the SMSs, whether daily, twice daily, or weekly, and the timing of the test messages (time per day/number per trimester). The data will be analyzed using SPSS version 30.0.

### 2.8. Ethical Considerations

The Human Research Ethics Committee at the University of Fort Hare (Ref #2024=02=05 [name]) approved the study protocol. Informed consent will be obtained from all participants before collecting data. Participants will be notified of their voluntary involvement and that they may withdraw at any time without prejudice. Furthermore, the participants’ confidentiality and privacy will be protected throughout. Only the researchers will have access to the recorded interviews. The researchers will conduct, analyze, and store both the qualitative and quantitative data in a cabinet until the completion of the research project using an interview guide. Similarly, the participant’s identity and information will remain hidden. Only the researchers will have access to the password-protected computer that has the data.

## 3. Discussion

The MomConnect device is devoid of physical activity and exercise content that would encourage physical activity during pregnancy. Therefore, this protocol outlines a research roadmap that outlines the steps involved in designing and developing a preferred prototype for prenatal physical activity and exercise text massaging. The developed prototype could potentially be integrated into the MomConnect technological health device to encourage women in the Eastern Cape Province of South Africa to engage in physical activity and exercise during pregnancy. This protocol study makes a unique contribution as the first to provide insights for designing physical activity and exercise content for the MomConnect device. The lack of awareness regarding prenatal physical activity and exercise constitutes a significant obstacle to physical activity engagement among women [20,23,24]. Consequently, enhancing women’s understanding of prenatal physical activity may significantly influence the adoption of such behavior. Engagement in prenatal physical activity can enhance clinical and maternal–child health outcomes [1,4,5,6,7,8,9,10,47]. Hence, efforts to encourage women’s physical activeness during and after pregnancy are crucial. The use of SMS messaging has the potential to create awareness and knowledge about prenatal physical activity and exercise.

Mobile health (mHealth) interventions demonstrate potential in enhancing maternal health outcomes, especially in resource-constrained settings. These interventions can improve access to maternal health information, promote health-seeking behaviors, and assist healthcare workers. A previous study in South Africa showed that text-message-based maternal mHealth interventions could provide pregnant women with timely, relevant, useful, and supportive information on birth preparedness and postnatal care [48]. Studies have shown that text messages encourage pregnant women to engage in more physical activity [37,49]. The interplay between content relevance and frequency may influence the effectiveness of text messages in promoting physical activity, with frequent irrelevant messages potentially reducing activity levels [50]. Irrelevant communication frequency can have a negative influence on physical activity, emphasizing the risk of providing irrelevant content in digital health strategies [50]. Therefore, contextually relevant prenatal physical activity SMS content could potentially be effective in encouraging physical activity among pregnant women when integrated into the MomConnect technological device. Once we have developed and designed the desired physical activity SMS specifically for pregnant women in this geographical setting, our study will provide the foundation to evaluate such a postulation. This study will emphasize the potential of mobile technologies to enhance physical activity among pregnant and postnatal women while also addressing the challenges associated with recruitment and sustaining engagement.

The findings of this study will assist in ascertaining the preferred dose of SMS messaging to promote prenatal physical activity and exercise among women. Similarly, the results of this study will provide the foundation for designing a randomized control trial to evaluate the effectiveness, efficacy, and acceptability of MomConnect in promoting prenatal physical activity among pregnant women within the framework of BCCM. If the MomConnect interventional approach proves effective, it could lead to a large-scale implementation among reproductive-age women in the province and across the country. Such information is necessary for strategic planning regarding the delivery of prenatal physical activity healthcare services. Finally, the findings of this study will assist policymakers in comprehending the significance of developing an innovative, low-cost intervention strategy to enhance prenatal physical activity and exercise, a frequently overlooked yet crucial aspect of antenatal healthcare.

